#### Plans to promote participant retention and complete follow-up {18b}

The PEx cohort is designed to be pragmatic and embedded within routine care to foster high participation and retention and minimize the burden on participants and clinicians. Data quality and adherence to the protocol is promoted by (i) conducting a commencement meeting for all project coordinators and investigators at each site prior to their involvement; (ii) performing site inductions which include specific training about the protocol and the provision of reference documents for project staff; (iii) provision of a data dictionary to assist with data entry on the CRF/eCRF; and (iv) the data management center performs timely validation of data and addresses queries and corrections if errors are found during quality control checks.

#### Data management {19}

Streamlined data collection instruments and procedures are used to optimize efficiency and minimize the burden on participating sites. All data are entered into an eCRF by trained project staff. The eCRF is accessed via a web-based Clinical Trial Management System (CTMS). An Australian based company, Research Path, have been contracted to supply a web-based CTMS. The CTMS is a secure application comprising a web-based user interface and associated hosted services (backend) such as the web and database servers. All communication between the user’s browser and database servers is encrypted end-to-end. The core hosted servers (web, database, files) are all located in Australia, conform to the International Organisation for Standardisation requirements (ISO 27001), the Health Insurance Portability and Accountability Act (HIPAA), and Service Organisation Control standards (SOC 2), and employ strict infrastructure security policies. Access to all infrastructure systems and services is controlled through strict security controls and two-factor authentication. All users have permissions defined by their user role type as designated by the sponsor.

The project manager, or delegate, performs regular and timely validation of data, queries, and corrections. Any common patterns of errors found during quality control checks are fed back to participating sites. Missing data are minimized through regular data monitoring and a clear and comprehensive data dictionary with online data entry including logic checks.

As the PEx cohort is intended to be perpetual, data will be retained indefinitely. In the case of closure of the project, the sponsor will retain an identical replica of the platform database for at least 25 years or longer as is required by the approving regulatory authorities.

#### Confidentiality {27}

Participant data are identified by a unique study identification number on all study documentation, including the database, to ensure confidentiality. All documents are stored securely on the CTMS and are only accessible by project staff and authorized personnel. The project complies with all laws pertaining to data protection.

In order to administer the ePRO while ensuring participant anonymity, participant contact details are stored encrypted in a separate database segregated from the ePRO results. Minimum contact data is collected to ensure follow-up can be completed, including name, email address, and mobile phone. Electronic consent data, which are identifiable, are captured and stored separately to all other platform data in a secure database which is hosted by the sponsor.

#### Plans for collection, laboratory evaluation, and storage of biological specimens for genetic or molecular analysis in this trial/future use {33}

The PEx cohort entails no collection or storage of biological specimens, but collection or salvage may be required by participation in nested sub-studies. Where relevant, any procedures for collection or salvage of biological specimens for any nested studies will be specified within their relevant subprotocols or appendices.

### Statistical methods

#### Statistical methods for primary and secondary outcomes {20a}

Individual demographics, baseline clinical characteristics (at enrolment and at the commencement of each PERIT), outcomes, and loss to follow-up are periodically reported for all PEx cohort participants. The proportion of participants with the primary endpoint measured, and any loss to follow-up, is assessed and reported. Categorical variables are summarized at each level as a frequency and proportion. Cell frequencies below five members are reported as “< 5” to ensure individual confidentiality. Continuous variables are summarized as mean and standard deviation for symmetric distributions and median and interquartile range (IQR) for asymmetric distributions.

Continuous, categorical, and time-to-event endpoints may be assessed using standard statistical analytical approaches (chi squared, Fisher’s exact, Student *t* test, and Mann-Whitney tests as appropriate). Predictors of treatment outcomes will be assessed using Bayesian regression methods for binary, continuous, and time-to-event endpoints as appropriate. All summary statistics, analyses, and data visualizations will be generated in R version 3.5.3 or a later version, which is provided open source by the R Foundation for Statistical Computing. Analyses are performed and reported by the therapy received and the prespecified patient strata defined below; however, outcomes may not be reported for any Interventions assigned in the PEx Treatment Platform or other sub-studies if this information would inform or impact ongoing comparative effectiveness evaluations. All other subgroup analyses will be reported as post hoc.

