### Interventions

#### Explanation for the choice of comparators {6b}

The PEx cohort is observational; therefore, no specific interventions are defined for this cohort. For the purpose of reporting a sub-study from the PEx cohort, a PERIT intervention is considered to be any treatment, procedure, or strategy used in the acute management of a PERIT. PERIT interventions in the sub-studies are grouped into therapeutic domains comprising sets of mutually exclusive interventions, for example, sets of backbone antibiotics, sets of adjunctive antibiotics, sets of mucolytic therapies, sets of alternative physiotherapeutic regimens, and sets of immunomodulator treatments.

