#### Outcomes {12}

The primary estimand (inferential target for estimation) for each participant, for each PERIT, is defined by:*Study population:* People with CF with a PERIT who can perform spirometry and for whom there is reasonable equipoise about the most appropriate first line treatment regimen*Primary outcome and endpoint:* The change in lung function 7–10 days after commencing intensive therapy (therapy entailing use of at least one intravenous antibiotic), measured as the absolute change in percentage predicted forced expiratory volume in 1-s (ppFEV_1_) from initiation of intensive therapy (measured closest in time to the first dose on IV therapy, *and not* ≥ 14 days before, *and not* ≥ 72 hours afterwards) to the first measured ppFEV_1_ ≥ 7 days afterwards (measured closest in time to 7x24 hours afterwards *but not* ≥ 10 days (10x24 hours) afterwards)*Primary effect measure:* The absolute difference in the mean of the primary endpoint between those in the intervention versus the comparator group, adjusting for any differences in baseline factors between intervention and comparator arms that might otherwise confound or reduce the certainty of the treatment effect*Interventions:* Prescription of each intervention within a domain*Comparators*: Prescription of each other Intervention within that domain*Intercurrent events:* Participants will be included in the primary analysis irrespective of whether and how the intervention or comparator is received, any non-adherence, any subsequent change in therapy, or loss to follow-up, (i.e., the effect attributable to the prescription, or the treatment policy or de facto estimand)

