### Data collection and management

#### Plans for assessment and collection of outcomes {18a}

PEx cohort data is collected on electronic and/or hard copy case report forms (eCRF/CRF) pertaining to (i) clinical and demographic data, (ii) disease characteristics (including pancreatic exocrine status, CF-related diabetes, genotype), (iii) anthropometric data (including height and weight), (iv) lung function, (v) PERITs including the treatment(s) received, serial lung function measurements at defined time points and laboratory and clinical outcomes, (vi) microbiological outcomes, and (vii) patient-reported outcomes. Tables 1 and 2 provide justifications for the collection of data in the PEx cohort, specific for individuals and PERITs, respectively. However, sub-studies may require the additional collection of these variables at different time points, which will be specified within the relevant subprotocols and appendices.

**Table 1 Tab1:** Outcome data for BEAT-CF participants

Category	Variable	Timing		Justification
		At cohort entry	3-monthly	
**Demographic data**	Date of birth	Y		Age is independently associated with baseline lung function in CF. There may be “cohort” effects whereby those born in more recent periods have better outcomes because of improvements in care
	Sex	Y		Sex is independently associated with lung function in CF
**Clinical**	Genotype	Y		Validation of CF diagnosis
	Sweat test results	Y		Validation of CF diagnosis
	Pancreatic exocrine status	Y	Y	Pancreatic function is independently associated with lung function in CF
	CF-related diabetes	Y	Y	Diabetes is independently associated with lung function in CF
	Known drug allergies or contraindications	Y	Y	Drug allergies and contraindications constrain therapeutic options, and plausibly confounds or modifies treatment effects
	Concomitant medications	Y	Y	Use of concomitant medications plausibly confounds or modifies treatment effects, including toxicities
**Laboratory**	Total IgE	Y^a^	Y	Marker for allergic bronchopulmonary aspergillosis which is a cause of clinical deterioration and may confound PEx management
	*Aspergillus*-specific RAST	Y^a^	Y	Marker for allergic bronchopulmonary aspergillosis which is a cause of clinical deterioration and may confound PEx management

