#### Methods in analysis to handle protocol non-adherence and any statistical methods to handle missing data {20c}

In the primary analyses, participants will be assessed according to the initially prescribed treatment, irrespective of intercurrent events, including whether and how treatments are received, non-adherence, changes to therapy, or loss to follow-up, i.e., the analysis will determine the effect attributable to the initial treatment plan, reflecting the de facto or “treatment policy” estimand.

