No clear consensus exists around the definition of PEx of CF and definitions that might fit adult patients do not necessarily fit children [23]. However, a clear association exists between the decision to prescribe intravenous antibiotics for treatment of pulmonary symptoms or signs and health outcomes. Hence, a clinician’s decision to treat with intravenous antibiotics is often used in clinical trials to define exacerbations [1, 23]. BEAT CF will therefore focus on pulmonary exacerbations requiring intensive therapy (PERIT) defined pragmatically as therapy comprising the initiation of at least one antibiotic by the intravenous route. This definition may need to be re-visited if evidence emerges for use of oral or inhaled antibiotic therapies without intravenous antibiotics.

We have followed the latest ICH statistical guidance (E9 (R1)) to specify analyses in the estimand framework [24]. In the estimand framework, each analysis needs to be explicit about the target of (causal) inference. At a minimum, this requires specification of (1) the analysis population (who is included and excluded?), (2) the outcome (what part of the patient experience are we trying to capture?), (3) the endpoint (what are we using as a valid measure of that outcome?), (4) the intervention (e.g., what treatment, range of doses, frequencies, durations can be considered to constitute the treatment in question?), (5) the comparator (e.g., what treatment or range of treatments, their doses, frequencies), (6) the summary of the treatment effect (how are we framing the contrast between investigational intervention and its comparator? e.g., relative risk, odds ratio, etc.), (7) the approach to handling intercurrent events (how will treatment non-completion and crossovers, loss-to-follow-up, missing endpoints, deaths, etc., be managed?). Here, we have prioritized the de facto estimand over the de jure estimand, meaning that we are implicitly prioritizing measurement of the effect of prescribing an intervention (or the “intention-to-treat”), over the effect of adhering to the prescribed intervention. By focusing on short-term endpoints after largely supervised therapy, we anticipate that the de facto estimand will approximate the de jure estimand, although we expect to observe some early treatment discontinuations and crossovers due to adverse reactions.

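### Section {20a} groups analyses by therapy received, which contradicts the treatment-policy estimand in {12} and the initial-prescription rule in {20c}

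*Protocol article*

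**What the plan says.** Four places in the protocol article bear on which treatment group an episode belongs to.

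- **Outcomes {12}**, primary estimand: the intervention is "Prescription of each intervention within a domain", and comparators are defined in the same way. Episodes are included "irrespective of whether and how the intervention or comparator is received, any non-adherence, any subsequent change in therapy". The article names the target as "the effect attributable to the prescription, or the treatment policy or de facto estimand".
- **Section {20c}**, on non-adherence and missing data: in the primary analyses, "participants will be assessed according to the initially prescribed treatment, irrespective of intercurrent events".
- **Discussion**: "we have prioritized the de facto estimand over the de jure estimand".
- **Section {20a}**, statistical methods for primary and secondary outcomes: "Analyses are performed and reported by the therapy received and the prespecified patient strata defined below".

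The first three agree with one another. The fourth does not agree with them.

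**The concern.** The cohort's primary objective is comparative effectiveness, so the rule that places an episode in a treatment group defines the contrast being estimated. Under {12} and {20c}, that rule looks only at what was prescribed at the start. Under {20a} as written, it looks at what was received, and that can depend on events after Day 0 such as poor response, an adverse reaction or a change of drug.

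If patients who do badly leave their starting group, the group they leave can look better and the group they join worse, with no real difference between treatments. If a real difference exists, mixing the groups can shrink it. The article also plans periodic reporting and serves as the top-level protocol for nested studies. Two analysts could each follow it faithfully and publish different estimates.

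**Working it through.** The article states no sample size, power, SD or switching rate, so there is no figure to reproduce. The check is textual, followed by an illustration on stated assumptions.

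**1. Does the {20a} sentence reach the primary analysis?** Its heading covers primary and secondary outcomes. It follows the sentences on hypothesis tests and Bayesian regression. It ties the grouping to the prespecified strata, which {20b} assigns to the primary and secondary analyses. No word limits it to descriptive, secondary or sensitivity use. As written, it reaches the primary analysis.

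**2. Do the rules differ in practice?** Take an episode prescribed option A at the start and moved to option B on day 4. Under {12} and {20c} it counts under A. Under {20a} it counts under B, or under both, since the sentence does not say how mixed exposure is classed. The rules agree only for episodes with no change.

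**3. Does the article expect changes?** Yes, without rates. The secondary endpoints in {12} count stopping before day 7 and before day 14, for adverse reactions or for poor response. The Discussion expects some early crossovers from adverse reactions. It also says clinicians often change therapy for poor response after 7–10 days, and gives this as a reason for the early primary endpoint.

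**4. How large could the effect be?** Assumptions, none from the article: two options prescribed 1:1 to exchangeable groups, no true difference, SD σ of the ppFEV1 change, early response correlated ρ with the endpoint, and the fractions s_A and s_B with the poorest early response switching to the other option before the endpoint.

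Let φ_A and φ_B be the standard normal density at the s_A and s_B quantiles (0 if nobody switches), and d = s_A − s_B. Per starting patient in each group, switchers from A contribute a total of −ρσφ_A and stayers +ρσφ_A; likewise for B. The as-received A group then has total ρσ(φ_A − φ_B) over 1 − d, and the as-received B group has minus that total over 1 + d. The difference is

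D = 2ρσ(φ_A − φ_B) / (1 − d²).

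For σ = 10, s_A = 0.10, s_B = 0, φ_A = 0.1755:
- ρ = 0.5: 2 × 0.5 × 10 × 0.1755 / 0.99 = 1.77
- ρ = 0.8: 2 × 0.8 × 10 × 0.1755 / 0.99 = 2.84

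A simulation of 2,000,000 episodes per scenario gave 1.79 and 2.83. Its results for σ = 10 were:

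| Switching, A / B | ρ = 0.5 | ρ = 0.8 |
|---|---|---|
| 2% / 0 | 0.49 | 0.77 |
| 5% / 0 | 1.05 | 1.66 |
| 10% / 0 | 1.79 | 2.83 |
| 20% / 0 | 2.91 | 4.66 |
| 10% / 5% | 0.72 | 1.15 |
| 10% / 10% | 0.00 | 0.00 |

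Across σ = 8 to 12, the 10% / 0 case ranges from 1.4 to 3.4. A second simulation with weaker selection (σ = 8, switching probability logistic in the response, slope 0.5 or 1.0 per SD, one group only) gave 0.72 to 1.35 at 10%.

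**5. Dilution.** Suppose a true 3-point difference stays with the initial prescription and a fraction s switches in each group. The as-received difference is 3(1 − 2s): 2.7 at 5%, 2.4 at 10% and 1.8 at 20%. The simulation gave 2.70, 2.40 and 1.82.

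**6. Grouping by initial prescription** gave differences within 0.04 of zero in every scenario with no true effect, and 3.00 to 3.02 when the true difference was 3. This holds because the simulated groups are exchangeable.

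**The case against.** The strongest reply is that the primary rule is already fixed, and more specifically, elsewhere. Outcomes {12} and {20c} settle it and the Discussion repeats it; against them stands one general sentence. That sentence goes on to restrict reporting for interventions assigned in sub-studies, so therapy received may simply mean usual care as opposed to assigned treatment. This is a possible reading, but the article does not state it. If {20c} is taken to govern the primary analyses and {20a} the rest, the secondary endpoints out to 180 days would be grouped by receipt, where switching matters most.

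Other parts of the reply stand and limit the point:

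- **Size and direction.** A reader might infer that receipt-based grouping must favour whichever regimen poor responders leave. That needs unequal, response-driven switching. The article gives no rates, and with equal switching and no true effect the bias cancels.
- **The primary endpoint.** It was placed early to precede most response-driven changes, and the Discussion attributes expected early crossovers to adverse reactions. Exposure there is limited, though not nil.
- **Immortal time.** A reader might extend this to the primary endpoint. It does not apply to a change score measured in a fixed window; it could matter for time to next PERIT.
- **Recording of the plan.** A reader might infer from {6b} ("any treatment, procedure, or strategy used in the acute management of a PERIT") and {18a} ("PERITs including the treatment(s) received, serial lung function measurements at defined time points") that the initial prescription is not captured. The first concerns sub-study reporting and the second is a condensed data list. The early-stopping endpoints in {12} refer to planned and prescribed therapy, so the article does not show a gap.
- **Unbiasedness of the alternative.** Grouping by prescription does not by itself remove bias in a non-randomised cohort; {12} itself calls for adjustment for baseline differences.

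**Conclusion.** The contradiction is real, and {20a} is wrong as written: following it would estimate a different contrast from the stated primary estimand. This conclusion rests on the text alone.

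The numerical consequence is conditional. Under the assumed SDs, correlations and one-sided switching, the spurious difference runs from under half a point to several ppFEV1 points; with equal switching it is about 0 under the null, and a true effect shrinks. None of these figures is an estimate for this cohort. The concern is modest at the day 7 to <10 primary endpoint and greater for the 14- to 180-day endpoints and time to next PERIT.

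**What to change.** In {20a}, replace the grouping by therapy received with grouping *by the intervention initially prescribed in each domain*, for all comparative analyses of primary and secondary outcomes. State that these analyses carry the baseline confounder adjustment that {12} already requires. Label any table by therapy received as descriptive or supplementary.

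The cost is one amended sentence and a table label. The documents give no ground for asking for a new data field, and clinical care does not change. For the primary analyses, the change only brings {20a} into line with {12} and {20c}; for the secondary outcomes, it makes explicit the priority stated in the Discussion.

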#### Interim analyses {21b}

Descriptive summaries of the PEx cohort and analyses will be periodically updated and reported. Any interim or scheduled analyses for any nested sub-studies will be specified a priori in their relevant subprotocols and appendices.

#### Methods for additional analyses (e.g., subgroup analyses) {20b}

The pre-specified strata for primary and secondary analyses for the PEx cohort are:ppFEV_1_ ≥ 70% in the preceding 12 months (365 days) or unable to perform spirometry (e.g., due to young age) and no known *Pseudomonas aeruginosa* colonization in the preceding 2 years (2*365 days)ppFEV_1_ ≥ 70% in the preceding 12 months (365 days) or unable to perform spirometry (e.g., due to young age) and known *Pseudomonas aeruginosa* colonization in the preceding 2 years (2*365 days).ppFEV_1_ < 70% in the preceding 12 months (365 days) and no known *Pseudomonas aeruginosa* colonization in the preceding 2 years (2*365 days)ppFEV_1_ < 70% in the preceding 12 months (365 days) and known *Pseudomonas aeruginosa* colonization in the preceding 2 years (2*365 days)

The number of strata within PEx cohort may be prospectively updated, depending on the impact of such decisions on precision. Other subgroup analyses may be performed and will be reported as post hoc.

#### Methods in analysis to handle protocol non-adherence and any statistical methods to handle missing data {20c}

In the primary analyses, participants will be assessed according to the initially prescribed treatment, irrespective of intercurrent events, including whether and how treatments are received, non-adherence, changes to therapy, or loss to follow-up, i.e., the analysis will determine the effect attributable to the initial treatment plan, reflecting the de facto or “treatment policy” estimand.

#### Plans to give access to the full protocol, participant level-data and statistical code {31c}

The current version of the full PEx Core Protocol will be accessible on the project website beatcf.org.au. Decisions regarding the sharing of de-identified data and/or statistical code will be assessed by the project Steering Committee and will be conditional upon any necessary institutional and ethics approvals and data sharing agreements.

